**Figure 2 Fig2:**
[figure not shown]
Alternative Summary-of-Findings (SoF) table format (Table A).

**Figure 3 Fig3:**
[figure not shown]
Current Summary-of-Findings (SoF) table format (Table C).

#### Randomization

Once the potentially eligible participants have completed the general information and background questionnaire, those who meet the selection criteria will be stratified according to self-reporting data as clinicians, guideline developers, or researchers and randomly allocated to one of the 2 SoF tables in a 1:1 ratio. To minimize missing data, the 'Survey Monkey' system will randomly assign participants to one of the SoF tables immediately after stratification, providing them with a link to access the questionnaires and tables.

#### Concealment of allocation

Since random allocation of participants to a SoF table is done automatically by the 'Survey Monkey' system in real time following an unknown algorithm, without a pre-specified sequence, it will be not known in advance to which group the next participant will be allocated. Therefore, in the trial allocation concealment is guaranteed.

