### Overview of the design

We will conduct a parallel-armed, non-inferiority randomized trial comparing a new alternative format of SoF tables with current format. We will contact systematic review users by Email and ask them to fill a questionnaire developed using the 'Survey Monkey' online system. The data collection form will include questions about baseline information (demographic characteristics, background, familiarity with systematic reviews and the GRADE system, and so on). Then, participants will be randomly assigned to one of two SoF tables, either the one in the alternative format or the one with the current format (See Figure 1). Randomization will be stratified according to participants’ background (health professional, guideline developer, researcher). They will be asked to answer questions to determine understanding, accessibility of information, and satisfaction with the table format to which they were allocated. Finally, we will show them the other table format to which they were not initially allocated in order to test their preference for either one.

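### Randomisation is described as stratified 1:1 with guaranteed concealment, but the allocation algorithm is stated to be unknown, so balance within strata is not shown and the guarantee does not follow

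*Protocol article*

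**What the plan says.** Under Overview of the design: "Randomization will be stratified according to participants’ background (health professional, guideline developer, researcher". The Randomization section repeats this. Eligible people are sorted into clinicians, guideline developers or researchers and "randomly allocated to one of the 2 SoF tables in a 1:1 ratio", and the survey system "will randomly assign participants to one of the SoF tables immediately after stratification".

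Concealment of allocation describes the mechanism. The system allocates in real time "following an unknown algorithm, without a pre-specified sequence", from which the protocol infers that "it will be not known in advance to which group the next participant will be allocated" and concludes: "Therefore, in the trial allocation concealment is guaranteed".

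No section mentions blocks, minimisation or any other restriction within strata. In the analysis, Inferential analysis lists participant strata as a potential predictor. Evaluation of the models keeps a predictor only if it moves the parameter estimate by more than 10%.

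**The concern.** Three properties are asserted: stratified balance, a 1:1 ratio and guaranteed concealment. All depend on how the platform allocates, and the protocol says that this is not known. This is not a detail condensed out of an article, because the text affirmatively states that the mechanism is unknown.

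- **Balance.** Sorting people into strata and then drawing independently for each person is simple randomisation under another name. Only a restriction within strata makes the strata count.
- **Concealment.** That the investigators do not know an algorithm does not make its output random or unpredictable. The stated reason does not support the conclusion.

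At stake is whether the arms can be relied on to have similar mixes of clinicians, guideline developers and researchers. Background is plausibly related to understanding, and the protocol itself lists it as a potential predictor. The difference in proportions correct is judged against a 10-point margin.

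**Working it through.** **Inputs from the protocol (Sample size calculation, Randomization).** 1:1 allocation; three strata; 280 participants, 308 with dropout; margin 10 points; one-sided 95% confidence interval; 80% power; 80 to 87% correct on the current format; no true difference.

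**Assumptions, not in the protocol.** Strata of 103, 103 and 102; independent fair draws where stated; correct rates of 92, 82 and 72% by stratum for the last step.

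**1. The plan's own figure.** Per arm, n = (1.645 + 0.842)² × 2p(1 − p) / 0.10². At p = 0.87 this is 6.18 × 0.2262 / 0.01 ≈ 139.9, so 140 per arm and 280 in total, which matches. At p = 0.80 the total would be 396. The calculation uses one overall proportion and takes no credit for stratification, so the planned power does not depend on it.

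**2. Balance under three mechanisms.** Between-arm difference in the share of one stratum, N = 308, 20,000 simulations:

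| Mechanism | SD (points) | 95th percentile of absolute difference (points) |
|---|---|---|
| Simple, no strata | 5.4 | 10.6 |
| Independent draws within strata | 5.3 | 10.3 |
| Permuted blocks of 4 within strata | 0.5 | 1.1 |

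The first two are the same process, and the gap between them is simulation error. A direct check gives 2 × √[(1/3)(2/3)/308] = 5.4 points.

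**3. Size of splits under independent draws.** The 95% range for one arm is 137 to 171 of 308 overall, and 42 to 61 in a stratum of 103. A split worse than 60:40 has probability 4.8% in a stratum of 103 and 3.7% in one of 102. For at least one of the three: 1 − 0.952 × 0.952 × 0.963 ≈ 13%. A stratum of only 30 would have a 20% chance.

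**4. Effect on power.** At 280 and p = 0.87, power is 80.0% with 140/140, 79.6% with 124/156, and 79.9% averaged over simple randomisation.

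**5. Effect on precision.** With 92/82/72% the mean is 82%.
- Total variance per person: 0.82 × 0.18 = 0.1476.
- Between-stratum part: (0.10² + 0² + 0.10²)/3 = 0.0067, which is 4.5% of the total.
- SE of the crude difference: √(0.1476 × 4/308) = 4.38 points.
- SE with stratum imbalance removed: √(0.1409 × 4/308) = 4.28 points, about 2% smaller.
- Imbalance component alone: √(0.0067 × 4/308) = 0.93 points, a 95% range of about ±1.8 points. It is already inside the 4.38, since 0.93² + 4.28² ≈ 4.38².

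**The case against.** The strongest case on the other side is that this is mostly wording.

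- **The algorithm may balance after all.** A dynamic or adaptive method has no sequence fixed in advance, yet it can balance arms within strata. This stands. A reader might infer that the stratification balances nothing, but the protocol does not say that draws are independent. Only the narrower statement is supported: balance is not shown.
- **Concealment is probably sound.** Allocation is automatic and in real time, after eligibility and baseline data are complete. No recruiter handles a list. This also stands. A reader might infer that a rotating platform would let the next assignment be guessed, for example at workshops where people enter one after another. Rotation is a conjecture, and the documents show no route by which anyone could see earlier allocations and exploit a pattern. The fault lies in the inference to a guarantee.
- **The numbers are small.** A reader might set the ±1.8 points against the 10-point margin and see a bias of nearly a fifth of it. That is not supported. It rests on invented stratum rates, and it is chance variation that an unstratified confidence interval already counts.
- **The model can adjust for strata.** This stands only in part. The 10% rule is applied separately in seven question-level models. The design expects a true effect near zero, where a percentage change in the estimate is unstable. An imbalance may trigger retention in one model and not in another, so adjustment is possible but not assured.

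**Conclusion.** The point holds in a limited form. The protocol claims stratified 1:1 allocation and guaranteed concealment for a mechanism that it says it does not know. Balance within strata is therefore not shown. If draws are independent, stratifying adds practically no balance: an SD of 5.3 to 5.4 points either way, against about 0.5 with blocks of 4, assuming three equal strata. Concealment is plausible, but the reason given does not guarantee it.

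The consequence is modest. Simple randomisation would be unbiased, the average power loss from unequal arms is about 0.1 percentage point, and removing stratum imbalance would shrink the standard error by about 2% under the assumed 92/82/72% rates. The sample size does not change. The correction is still worth making, because the allocation method underpins a randomised comparison and the 10% retention rule does not reliably make up for the gap.

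**What to change.** 1. For participants still to be recruited, generate a computer permuted-block list for each of the three strata, with varying block sizes and hidden from recruiters. Have the survey logic draw the next entry from it, if the platform can do this. Record when the mechanism changed.
2. If the platform cannot, establish how it allocates from its documentation and a batch of test entries. Test entries can reveal rotation, but they cannot prove independence. Then correct Overview of the design, Randomization and Concealment of allocation to the actual mechanism, which is simple randomisation if draws are independent.
3. In either case, replace the guarantee of concealment with the verified reason why the next allocation cannot be foreseen.
4. In either case, keep participant strata in every outcome model and exempt them from the 10% retention rule.

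The cost is some set-up work while recruitment is open, or a wording correction and test entries. Keeping strata uses two model parameters.

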#### Blinding

The data collection process will be conducted automatically by the 'Survey Monkey' web platform. The SoF table formats will be labeled as A, or C; thus, participants will be allocated to Table A or C without any other information about the nature of the tables. Participants will be blinded to whether the table they are exposed to was the one in the current or alternative format while the outcomes understanding, accessibility, and satisfaction, are assessed. The only exception will be the outcome preference, as the only way to measure it is comparing the table to which they are randomized with the table to which they were not allocated. Therefore, participant blinding will be broken only after they have fully assessed the SoF table to which they were initially randomized. Once the data collection process is completed, the database will be prepared for statistical analysis and interpretation in a blinded fashion. Finally, the labels will be revealed after the analysis is done.

### Outcomes

The outcome assessments will be defined and conducted as follow:

#### Primary outcome

##### Understanding

It is defined as the correct comprehension of key findings. We will frame seven multiple-choice questions about key concepts in the table with five response alternatives for each question and only one correct answer. We will compare the proportion of correct answers between groups per question. A 10% difference was defined as the minimal important difference between groups.

#### Secondary outcomes

##### Accessibility of information

This outcome considers 3 domains: (1) how easy it is to find critical information in the table; (2) how easy it is to understand the information, and (3) whether the information is presented in a way that is helpful for decision-making. These three domains will be measured by presenting participants with 3 statements for which they have to indicate the degree of agreement: 'It was easy to find the information about the effects'; 'It was easy to understand the information', and 'The information is presented in a way that would help me making a decision'. Agreement will be measured using a 7-point Likert-type scale (1 = I strongly disagree, 2 = I disagree, 3 = I somewhat disagree, 4 = Neither agree nor disagree, 5 = I somewhat agree, 6 = I agree, and 7 = I strongly agree). The outcome overall accessibility of information will be measured directly using a 5-point Likert scale (1 = Very inaccessible, 2 = Inaccessible, 3 = Neither inaccessible nor accessible, 4 = Accessible, 5 = Very accessible), asking the participant to consider the 3 above domains together. For all these measures, we will compare the means per group in each domain and overall.

##### Satisfaction

Measured at an item level, we will ask participants which formatting features satisfy them the most (for example, 'In Table A, we included a column called 'What happens'. The purpose of this column is to assist users on the interpretation of both review results and quality of the evidence. Do you think this column should be included as an available feature in future versions of SoF tables?'). It will be measured as a dichotomous outcome and we will compare proportions per group.

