**Table 2 Tab2:** **Overview of outcome measures**

**Outcome measures**	**Scale**	**Measure**	**Analysis method**
Primary			
Understanding	Dichotomous	% of participants with correct answers	Multiple logistic regression
Secondary			
Accessibility of information (at a domain level)	Ordinal (treated as continuous)	1-7 Likert scale	Multiple linear regression
Overall accessibility of information	Ordinal (treated as continuous)	1-5 Likert-type scale	Multiple linear regression
Satisfaction	Dichotomous	% of participants satisfied with an item	Chi-square test
Preference	Continuous	1-7 Likert scale	Multiple linear regression

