### Inferential analysis

The primary outcome (understanding) will be estimated as the proportion of participants correctly answering each question per group. Data regarding this outcome will be analyzed using a multiple logistic regression per question, where the main predictor will be the arm to which participants were allocated (dichotomous - 2 categories). Other potential predictors to include in the model are participant strata (nominal - 3 categories), years of experience (nominal - 5 categories), familiarity with the GRADE approach (dichotomous - 2 categories), and previous education in health research methodology or epidemiology (ordinal - 3 categories). To adjust for multiplicity, the *P*-value will be modified using the Bonferroni correction for 7 multiple comparisons (<0.0035, CIs will be constructed with corresponding 1-sided z score 2.7).

For the secondary outcome, accessibility of information, we will calculate means, SDs and 95% CIs per domain. Data regarding this outcome will be analyzed using multiple linear regression where the main pre.dictor will be the arm to which participants were allocated (dichotomous - 2 categories). Other potential predictors included in the model will be participant strata (nominal - 3 categories), years of experience (nominal - 5 categories), familiarity with the GRADE approach (dichotomous - 2 categories), and previous education in health research methodology or epidemiology (ordinal - 3 categories). To adjust for multiplicity, the *P*-value will be modified using the Bonferroni correction for 4 multiple comparisons (<0.0125).

The secondary outcome, satisfaction, will be measured at an item level. The proportion of participants satisfied with either item included in Table A or C will be calculated per group.

For the secondary outcome, preference, linear regressions will be used. Since this outcome is obtained from a direct comparison of the tables (blinding is disclosed), there will be no main predictor of interest. However, we will control for the order in which the tables were shown to the participants (dichotomous - 2 categories). Other potential predictors to include in the model will be participant strata (nominal - 3 categories), years of experience (nominal - 5 categories), familiarity with the GRADE approach (dichotomous - 2 categories), and previous education in health research methodology or epidemiology (ordinal - 3 categories).

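### For features found in only one table, the planned between-arm chi-square on satisfaction does not measure satisfaction with the allocated format, and the example item conflicts with the blinding statement

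*Protocol article*

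**What the plan says.** The Overview of the design has participants answer on understanding, accessibility and "satisfaction with the table format to which they were allocated". The next step is: "Finally, we will show them the other table format to which they were not initially allocated in order to test their preference for either one". The Blinding section agrees with this order. It says "Participants will be blinded to whether the table they are exposed to was the one in the current or alternative format" while understanding, accessibility and satisfaction are assessed, and it makes preference the only exception.

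The Satisfaction section defines the outcome at item level. Its one example begins "In Table A, we included a column called 'What happens", explains what the column is for, and then asks "Do you think this column should be included as an available feature in future versions of SoF tables". On analysis it says "It will be measured as a dichotomous outcome and we will compare proportions per group". Table 2 gives the measure as the percentage "of participants satisfied with an item" and the method as a chi-square test. The Inferential analysis section adds: "The proportion of participants satisfied with either item included in Table A or C will be calculated per group". The section on claiming non-inferiority says that secondary outcomes are tested for superiority.

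**The concern.** A between-arm comparison needs the same question, asked about something that each arm has experienced. Here the protocol's own example asks about a column that half of the participants will not have seen at that point. A chi-square on such an item will still return a p-value, and under the plan it would be read as evidence on satisfaction with the two formats.

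The item wording also sits badly with the blinding statement. The tables are meant to carry only the labels A and C. An item that names Table A, points to one of its columns, gives its purpose and asks about future SoF tables suggests to the participant which table is the modified one.

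At stake are the interpretation of one secondary outcome for some of its items, and the accuracy of the blinding claim for that outcome.

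**Working it through.** The protocol gives no figure for satisfaction, so the main check sets the sections side by side.

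**1. Timing.** The Overview of the design and the Blinding section both put satisfaction before the second table is shown. When the items are answered, each participant knows one table.

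**2. Which features have a counterpart (Table 1 of the protocol).**

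| Row | Feature | In A | In C |
|---|---|---|---|
| 1 | Numbers of participants and studies | within the outcomes column | own column |
| 2 | Quality of evidence | with main reasons in the cell | symbols and label, reasons in footnotes |
| 3 | Label for notes | Explanations | Footnotes |
| 4 | Risks | percentages | natural frequencies |
| 5 | Risk or mean difference column | yes | no |
| 6 | Comments column | no | yes |
| 7 | 'What happens' column | yes | no |
| 8 | GRADE definitions under the table | no | yes |

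Rows 1 to 4 have a version in each table. Rows 5 to 8 are present or absent: two features are in A only (5 and 7) and two in C only (6 and 8). That is 4 of 8 rows.

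**3. Who rates what, for rows 5 to 8.** The Inferential analysis sentence fits two readings.

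- *Each arm rates the features of its own table.* The A arm might rate the 'What happens' column and the C arm the comments column. The chi-square then compares two different items.
- *Both arms receive the same item.* The item is common, but for row 7 the C arm judges a column it has only had described. The contrast is endorsement after use against endorsement on description.

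Neither is satisfaction with the allocated format compared between arms.

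**4. Illustration of the first reading.** The approval rates here are assumed; the protocol gives none. The group size is the planned 280 divided by 2, or 140 per arm. The 280 itself can be reproduced at 87% correct in both arms: (1.645 + 0.842)² × 2 × 0.87 × 0.13 / 0.10² = 139.9, so 140 per arm. It has no other bearing on this point.

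Power of a two-sided 5% chi-square test, with p̄ the mean of the two rates:

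Φ{ (|p₁ − p₂|√n − 1.96√[2p̄(1 − p̄)]) / √[p₁(1 − p₁) + p₂(1 − p₂)] }

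For 60% against 75%: (0.15 × 11.832 − 1.96 × 0.662) / 0.654 = 0.73, so the power is about 77%.

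| Approval of the two items | Chance of a significant result |
|---|---|
| 60% and 70% | 42% |
| 60% and 75% | 77% |
| 50% and 70% | 93% |

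If two different items simply differ in popularity by 10 to 20 points, the test often declares a difference between arms that says nothing about format on a common endpoint.

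**5. Blinding.** The Blinding section says participants do not know, during the satisfaction items, whether their table is the current or the alternative one. The example item attaches a named column to Table A and asks about future SoF tables. A participant in either arm can infer from it that A is the modified format. As written, the statement does not hold for this item.

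**The case against.** The strongest reply is that this generalises from one example. The full item list is not shown, a condensed article may leave it out, and rows 1 to 4 can be compared between arms. That stands. A reader might infer that the whole satisfaction outcome is uninterpretable, and the protocol does not support that.

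A second reply is that the chi-square need not compare unlike items. If both arms receive the same question, the contrast is a valid randomised comparison of those who used a feature with those who had it described. This also stands, and a reader should not conclude that different items are necessarily being compared. But that contrast still answers a different question from the stated one, satisfaction with the allocated table, and the protocol does not say that this is what it intends.

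Third, the item says the column was included, not that it was newly added, and the same verb could introduce a Table C feature. That is fair: the signal comes from naming Table A together with the reference to future tables, in a single example. It is nevertheless the only item the protocol offers.

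Fourth, the wording might be thought to invite agreement. That is conjecture. With identical wording in both arms, such an effect would mainly raise the overall level and need not distort the contrast.

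Finally, satisfaction is one secondary outcome and plays no part in the non-inferiority claim. That stands and limits the weight of the point.

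**Conclusion.** The point holds for the one-table features, rows 5 to 8, which are half of the listed differences. For these, the planned arm comparison is not interpretable as satisfaction with the allocated format on either reading of who rates what. The blinding statement and the example item also conflict and must be reconciled.

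A reader might go further and infer that understanding is affected by unblinding. The protocol does not support this: it lists satisfaction after understanding and accessibility, so nothing shows that either outcome is touched.

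The verdict assumes that the survey follows the order in the Overview of the design and that the example item is typical of the one-table items. The significance rates in the illustration depend on assumed approval rates and show only the direction of the problem; the effect of the wording cannot be quantified from the protocol. The change is worth making, because the plan as written would give a misleading result for these items.

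**What to change.** - State which items each arm rates.
- Ask the items on rows 5 to 8 of all participants after both tables have been shown, in neutral wording. Report the overall proportion with a 95% CI, and show results by arm only as a check on order.
- Limit the chi-square in Table 2 to identical, neutral items about features that both tables have (rows 1 to 4).
- Reword the example item so that it does not identify the modified table, or remove satisfaction from the blinding statement.
- If the live survey already shows both tables before the satisfaction items, correct the Overview of the design and the Blinding section instead.

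The cost is some reordering and rewording of survey items and a change to one line of Table 2. The real downside is that recruitment is under way. Responses before and after the change do not measure the same thing, so the earlier ones must be flagged and reported separately, with their one-table items descriptive only.

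### Satisfaction is compared with an unstratified chi-square test although randomisation is stratified by background; the test is valid but gives up some precision if satisfaction differs between strata

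*Protocol article*

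**What the plan says.** **Design.** Overview of the design states "Randomization will be stratified according to" participants' background. The Randomization section says that eligible participants are "stratified according to self-reporting data as clinicians, guideline developers, or researchers and randomly allocated" 1:1. Concealment of allocation describes the platform's method as "following an unknown algorithm, without a pre-specified sequence". No blocks within strata are mentioned.

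**Satisfaction.** The Satisfaction section says "It will be measured as a dichotomous outcome and we will compare proportions per group". Table 2 gives the measure as the percentage "of participants satisfied with an item" and the method as "Chi-square test". The Inferential analysis section adds only this: "The proportion of participants satisfied with either item included in Table A or C will be calculated per group". It names no covariate, stratum term or significance level for this outcome.

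**Other outcomes.** Understanding, accessibility and preference get regression models, with participant strata among the potential predictors. Under Evaluation of the models, a predictor stays only if it changes the key estimate by more than 10%.

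**The concern.** An analysis should normally reflect the factor used to stratify randomisation. If arms are balanced within background groups and satisfaction differs between those groups, the design has already removed the between-group variation from the comparison of arms. A plain chi-square test still counts that variation in its standard error, so it is conservative. If arms are not balanced within groups, the standard error is right on average. The crude difference then carries noise from chance imbalance in background, which a stratified estimate would remove.

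At stake is some power and some interval width for an item-level secondary outcome. The primary non-inferiority conclusion is not affected.

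**Working it through.** **The plan's own figure.** The article gives no sample size, power or precision for satisfaction. Its only such figure is 280 evaluable participants for understanding. That reproduces at 87% correct, a 10% margin, one-sided alpha 0.05 and 80% power: n per arm = (1.645 + 0.842)² × 2 × 0.87 × 0.13 / 0.10² ≈ 139.9, so 140 per arm and 280 in all. It is used below only to set 140 per arm.

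**Inputs that had to be assumed.** These are the satisfaction rates by background, equal stratum sizes, balance by arm within strata, and a two-sided 0.05 level. None is in the article, so a range of rates is shown.

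**Formula.** Let p_k be the rate in stratum k and p̄ the mean rate. With n per arm and balanced strata:
- variance used by the unstratified comparison: (2/n) × p̄(1 − p̄)
- variance used by the stratified comparison: (2/n) × mean of p_k(1 − p_k)
- SE ratio (unstratified/stratified): square root of p̄(1 − p̄) / mean[p_k(1 − p_k)]

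**Results.**

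| Assumed rates by stratum | p̄(1 − p̄) | mean p_k(1 − p_k) | Variance ratio | SE ratio |
|---|---|---|---|---|
| 70/70/70% | 0.2100 | 0.2100 | 1.000 | 1.000 |
| 65/70/75% | 0.2100 | 0.2083 | 1.008 | 1.004 |
| 60/70/80% | 0.2100 | 0.2033 | 1.033 | 1.016 |
| 50/70/90% | 0.2100 | 0.1833 | 1.145 | 1.070 |
| 30/60/90% | 0.2400 | 0.1800 | 1.333 | 1.155 |

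With 140 per arm, the unstratified SE at a mean rate of 70% is √(2 × 0.21/140) = 0.0548. The stratified SE is 0.0539 at 60/70/80% and 0.0512 at 50/70/90%. The last case is like losing 1 − 1/1.145 = 12.7% of participants, about one in eight.

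**Simulation.** There were 200,000 runs per scenario, with strata of 47, 47 and 46 in each arm. Power is for a 15-point difference added in every stratum.

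| Assumed rates | Type I error, chi-square | Type I error, CMH | Power, chi-square | Power, CMH |
|---|---|---|---|---|
| 60/60/60% | 0.049 | 0.048 | 77.1% | 76.9% |
| 50/60/70% | 0.045 | 0.050 | 77.2% | 77.9% |
| 40/60/80% | 0.037 | 0.050 | 78.3% | 82.1% |
| 30/55/85% | 0.026 | 0.051 | 77.9% | 84.7% |

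The chi-square test never exceeds 5%; it becomes conservative as the strata diverge. Stratifying costs almost nothing when the strata do not differ.

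**If strata are not balanced by arm.** Both tables assume balance. Under simple allocation within strata, p̄(1 − p̄) is the right variance for the crude difference, so the chi-square test keeps its nominal size. What is lost is only the precision that a stratified estimate could have gained.

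**The case against.** The strongest case against is that nothing here is an error. A chi-square test on randomised arms is valid, and a stratified test is an efficiency preference. The article does not say that satisfaction varies by background. For a spread of up to 20 points the cost is under 2% of the standard error, and the 7% figure needs an assumed 40-point spread. Satisfaction carries no stated significance level or decision rule and reads largely as feedback on features. An article may also leave the form of a test to a fuller document.

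Most of this stands and sets the size of the point. The last argument does not remove it: Table 2 names a test, and neither the table nor the text gives satisfaction a stratum term.

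A reader might infer more than the article supports:
- **That false positives are at risk.** They are not; the error rate is nominal or below. Chance imbalance in background is not bias, because the test's error rate already allows for it.
- **That precision is lost whatever the data show.** The loss depends on satisfaction differing by background, and it is nil if it does not.
- **That every other outcome is adjusted for the stratum.** Elsewhere the stratum is only a candidate. In a linear model with arms balanced within strata, adding it leaves the arm estimate essentially unchanged, so the 10% rule would tend to drop it.
- **That the standard error is certainly overstated.** This needs balance within strata, which an unknown algorithm with no stated blocks does not assure.

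**Conclusion.** The point holds as a minor one. Randomisation is stratified by background, and the comparison of satisfaction is fixed as an unstratified test with no place for the stratum. The consequence is a possible loss of efficiency, with validity intact. It ranges from nothing to about 7% of the standard error for assumed spreads of up to 40 points between equal strata balanced by arm, and is larger only for more extreme spreads. Satisfaction differs from the modelled outcomes only in that the stratum cannot enter at all; no analysis in the article is bound to keep it.

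**What to change.** In the satisfaction row of Table 2 and the satisfaction paragraph of Inferential analysis, replace the chi-square test with a Cochran-Mantel-Haenszel test stratified by background. Report a Mantel-Haenszel risk difference with its confidence interval for each item. State that the stratum is kept regardless of the 10% change-in-estimate rule; a sentence to that effect under Evaluation of the models would treat the modelled outcomes in the same way.

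The cost is a few lines of text. No new data are needed, because background is recorded before randomisation, and the stratified test loses practically no power if the strata turn out alike (76.9% against 77.1% in the simulation).
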